### Patient and public involvement

Patients were involved in the planning and development of the study protocol. A series of in-depth semi-structured interviews were conducted with the qualitative purpose of exploring the experiences acquired during the treatment course of a humeral shaft fracture. Beyond the qualitative study aim, a discussion of the most meaningful primary outcome measures was undertaken. All patients completed two questionnaires (DASH and QuickDASH) to solicit their feedback and to determine which PROM they found most appropriate when considering relevance, comprehensibility, comprehensiveness, and length. The interviews further revealed complaints that were discussed with the patients and were subsequently priorities to be implemented as outcome measures of the trial.

One of the patients from the interviews accepted to be involved in the trial as the PR. The PR is included in the steering committee and in the DMC. The study protocol was discussed with the PR in layman’s terms to facilitate a common understanding of the trial and to solicit feedback that could minimize patient burden and risk of missing data, as well as providing insights from a patient perspective to optimize the communication between physicians and patients during the trial course and by written information. The feedback resulted in minor revisions of words in the patient information sheet to conform with patient concerns.

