### Interim analyses

We will carry out two interim analyses after trial completion of 25% and 50% of the planned number of included patients, separately for the two age groups. We will use the O’Brien-Fleming rule [37] for determining appropriate significance levels for each analysis, which is determined by time of hypothesis testing (*n*=3) and the overall significance level of *α*=0.05. Under these assumptions, the significance levels are 0.0006 for the first interim analysis, 0.0151 for the second interim analysis, and 0.0471 for the final analysis. Interim analyses will be carried out for both the primary endpoint (DASH) and for serious complications (iatrogenic nerve injury, deep infection, major adverse cardiac events (MACE), other major adverse events, and death) and will be conducted by one-sided tests to determine if the improvement in DASH is significantly above 25 points, respectively if the complication rate is at least 20% higher.

A Data Monitoring Committee (DMC) has been organized to monitor and evaluate the data from the interim analyses. The DMC consists of five independent members including the patient representative (PR), two orthopedic researchers, an orthopedic surgeon, and a nurse.

In the event of one group having zero complications, the significance level cannot be computed by a cChi-square test, and the DMC will have to assess the data due to a statistical variation.

In the event of a patient sustaining several complications, the most severe complication will follow the patient. The complications are ranked in a hierarchy model describing the severity and are ranked from most severe to least severe: death, MACE, deep infection with debridement, other reasons for hospitalization, and iatrogenic nerve injury.

The interim analyses will be conducted by a biostatistician, blinded to the treatment allocation. Data will then be presented to the DMC, in means and proportions and be accompanied with confidence intervals. The DMC will have access to the data unblinded, and if at least one of those two conditions is fulfilled or a statistical variation has occurred at an interim analysis the DMC will be asked to investigate the results in detail and present their recommendation to continue or stop the trial. In the event of disagreement with a split decision (one or more casts a blank vote), the steering committee will be involved in discussing the stopping of the trial.

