Furthermore, the steering committee will be monitoring recruitment and drop-out. Any modification in design and recruitment will be registered on ClinicalTrials.gov.

If it is observed that inclusion of patients in the two age groups is too slow, it can be decided to pool the age groups and analyze them as one total group instead. If this decision is made before the first interim analysis, the above significance levels will be used for the total group. If the decision is made between the first and second interim analysis, O’Brien-Fleming significance levels for four analyses will be used, resulting in a significance level of 0.0184 for the second interim analysis and 0.0412 for the final analysis. If the decision is made after the second interim analysis, the O’Brien-Fleming significance level for five analyses will be used, resulting in a significance level of 0.0417 for the final analysis.

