### Sample size

The two groups (SHAFT-Y and SHAFT-E) require individual sample size calculations. Two standard deviations (SDs) were obtained from the data of the FISH trial [13] and were separated in age groups of 18–64 years and 65 years and above. By the distribution-based approach, one half a SD corresponds to the minimal important change (MIC) [49]. The calculations are powered to detect a MIC of 7 points in the young and 10 points in the elderly group in DASH, respectively. Two independent means sample size calculations were performed. For SHAFT-Y the following data were included: mean difference = 7.0, SD= 14.91, *α*= 0.05, and power= 0.8. For SHAFT-E the following data were included: mean difference= 10.0, SD= 18.59, α= 0.05 and power= 0.8. Based on the preceding assumptions and including an attrition of 15%, the total sample size is estimated to 163 patients for SHAFT-Y and 124 patients for SHAFT-E.

The FISH trial [13] experienced 5% attrition, since more sites are involved in SHAFT the attrition is set to 15%.

The steering committee can decide to pool data from both RCTs (SHAFT-Y, SHAFT-E) if recruitment is prolonged.

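### One DMC member described as independent, the patient representative, also sits on the steering committee that may pool the two age-group trials after unblinded interim looks

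*Protocol article*

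**What the plan says.** The section Interim analyses describes the committee: "The DMC consists of five independent members including the patient representative (PR), two orthopedic researchers, an orthopedic surgeon, and a nurse". It plans two looks, at 25% and 50% of the planned patients, carried out separately for each age group. The biostatistician is blinded, but of the committee it says: "The DMC will have access to the data unblinded".

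The section Patient and public involvement says: "The PR is included in the steering committee and in the DMC".

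The section Sample size gives the steering committee a design power: "The steering committee can decide to pool data from both RCTs (SHAFT-Y, SHAFT-E) if recruitment is prolonged". The section Interim analyses sets out when pooling may be decided: before the first look, between the two looks, or later. The last case begins: "If the decision is made after the second interim analysis". It names slow inclusion as the ground and gives no figure for it.

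Two further steering-committee roles matter. If the DMC is split, and one blank vote is enough, "the steering committee will be involved in discussing the stopping of the trial". Under Trial status, the same committee will discuss extending the study period if 287 patients have not been reached.

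**The concern.** A person who helps to govern a trial is not independent of the body that governs it. The two descriptions of the patient representative therefore do not fit together as written.

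This matters more here than in a trial with a fixed design, because the steering committee keeps a discretionary choice that bears on the primary analysis. Pooling replaces two separate age-group comparisons with one combined comparison. It changes the population, the hypothesis tested and the significance level. Such a choice is safe when the people making it do not know how the arms compare in each age group, and that is what the interim analyses show to the DMC. With a shared member, the trial loses the simplest evidence that a late pooling decision was made blind to results.

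**Working it through.** No stated figure depends on this point, so the check sets the passages side by side.

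1. **Membership.** The listed DMC members are 1 patient representative + 2 researchers + 1 surgeon + 1 nurse = 5, which matches the stated number. The word independent covers all five. Patient and public involvement places one of these five on the steering committee, so the overlap is 1/5 of the DMC. Trial design describes the steering committee as trauma and shoulder-elbow surgeons and does not list the representative, so that description also needs reconciling.

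2. **What the shared member would know.** The DMC sees unblinded data by age group. With 163 patients planned in SHAFT-Y and 124 in SHAFT-E:
   - first look: 0.25 × 163 = 40.75 (about 41) and 0.25 × 124 = 31 patients;
   - second look: 0.50 × 163 = 81.5 (about 82) and 0.50 × 124 = 62 patients.

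   After the second look, the representative would have seen the arm comparison in about half of each trial.

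3. **What the steering committee may still decide.** Sample size names it as the body that can pool. Interim analyses allows that decision between the looks and after the second one, and gives no latest date. The ground is slow recruitment, without a threshold, so deciding that the ground is met is a judgement.

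4. **What the adjusted levels cover.** Without pooling the final level is 0.0471.
   - Pooling between the looks: levels for four analyses, final level 0.0412.
   - Pooling after the second look: levels for five analyses, final level 0.0417.

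   These levels pay for extra tests. They take the decision to pool as unrelated to the results, so they give no protection if it was made because the results favoured one presentation over the other.

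5. **The split-vote route.** The DMC is asked for a recommendation only if an efficacy or complication condition is met, or if what the protocol terms a statistical variation has occurred (one group without complications). A referral to the steering committee therefore shows that one of these happened, even if no figures are passed on. A single blank vote can cause it, and the representative would sit on both sides of the referral.

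Nothing in the document has the representative step back from either committee. A charter that is not shown could add confidentiality or recusal rules. Confidentiality alone would not remove the conflict, because one person holds both roles.

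**The case against.** The strongest defence is that pooling has a recruitment trigger, stated in two sections, and does not depend on results. The significance levels are tightened when pooling follows a look, and any change in design is to be registered. Recusal and closed-session rules normally belong in a DMC charter or the full protocol, which a journal article condenses. Harm would require the representative to disclose or act on what was seen, and the steering committee to follow.

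Much of this stands. The missing charter detail is no fault of the article, and no passage suggests misuse. What remains are two positive statements that conflict, and a trigger loose enough that the decision makers' knowledge matters.

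Four stronger readings are tempting, and the document does not support them:

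- A reader might infer that the DMC as a whole is not independent. The overlap is shown for one member only.
- A reader might infer that the steering committee receives unblinded results on a split vote. The text says only that it takes part in discussing whether to stop; what it learns for certain is that a condition or a statistical variation occurred.
- A reader might treat extension as a further threat to the type I error. The text says extension will be discussed if the planned 287 patients have not been reached. More time to reach a fixed number is not in itself a data-driven increase in sample size.
- A reader might conclude that the type I error is inflated. That holds only if interim knowledge shaped the pooling decision.

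**Conclusion.** The point holds as a contradiction about one of five DMC members, joined to a pooling power that stays open after unblinded looks. The consequence is a loss of credibility for any pooled result: the trial could not demonstrate that the decision was blind to the arm comparison by age group. Any effect on the type I error is conditional on what was disclosed or acted on, and the document gives no basis for a figure.

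The conclusion assumes that the same representative attends the unblinded DMC review and takes part in steering-committee decisions, which is the plain reading. If pooling is never used, or is decided before the first interim analysis, the concern about the primary analysis falls away. The independence statement would still need correction. This should be put right before the first interim look, but it does not call the design as a whole into question.

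**What to change.** 1. Have the patient representative serve on only one of the two committees. Alternatively, exclude the representative from steering-committee decisions on pooling, extension and stopping once interim data have been seen.
2. State that pooling is decided on recruitment counts by people without access to interim results.
3. If the dual role is kept, correct the word independent in the section Interim analyses and describe the overlap.

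The cost is a change of membership or a recusal rule, plus a few sentences in the protocol. The drawback is that the patient voice is lost on one committee, or in those particular decisions, unless another of the interviewed patients agrees to serve. How a split DMC vote is resolved is a matter of governance preference, and no particular voting rule is needed to settle this point.

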### Interventions

Treatment will be performed within 14 days after injury. Eligible patients will be randomly allocated to one of two treatment options.Surgical treatmentNon-surgical treatment with the option of early crossover surgery at 6–12 weeks [17] for SHAFT-Y and at 12–26 weeks for SHAFT-E

We anticipate that surgical treatment will include plate osteosynthesis (minimal invasive plate osteosynthesis or open reduction internal fixation), intramedullary nailing (antegrade and retrograde), and external fixation. Plate and nail types, screw configurations, and surgical approaches will be decided by the surgeons. The procedure will be conducted or supervised by a senior consultant.

Non-surgical treatment will include sugar tong splint, plaster splints, hanging casts, or functional bracing such as the Sarmiento brace and will be worn until a surgeon removes it.

All patients will be advised to follow this rehabilitation protocol (Table 1).

**Table 1 Tab1:** Rehabilitation protocol

Phases (approx. timepoints)	Treatment (mobilization)	Explanation
**Non-surgical**		
Phase 1 Emergency department (ED) (0 weeks)	Apply immobilization device. (Wrist and fingers are recommended to be moved within immobilization device for anti-edema).	Immobilization device should not be taken off (dressing, hygiene). Await decrease of swelling and acute pain
Phase 2 (0–2 weeks)	Shift to brace, if not applied in ED. Physiotherapy can be introduced. (Unrestricted and unloaded active range of motion within the limitations of the brace are allowed).	Brace should always be carried. Patients allowed to lift objects, equivalently to a can of milk (max 1 kg). Physiotherapy can be started to introduce simple movements.
Phase 3a (6 weeks, can be extended to a maximum of 12 weeks)	Fracture is tested gently for instability in patients 18–64 years. If stable, continue to phase 4. If unstable or uncertain stability, return to phase 2 and extend period with brace or consider early crossover surgery.	a. The fracture is not sufficiently healed and needs more time with brace treatment. b. The fracture is grossly unstable and there is a risk of nonunion. Surgical fixation could be beneficial.
Phase 3b (12 weeks, can be extended to a maximum of 26 weeks)	Fracture is tested gently for instability in patients ≥ 65 years. If stable, continue to phase 4. If unstable or uncertain stability, return to phase 2 and extend period with brace or consider early crossover surgery.	a. The fracture is not sufficiently healed and needs more time with brace treatment. b. The fracture is grossly unstable and there is a risk of nonunion. Surgical fixation could be beneficial.
Phase 4 (Patients < 65 years: 6–12 weeks) (Patients > 65 years: 12–26 weeks)	Brace is removed. Continue physiotherapy. (Unrestricted active range of motion of shoulder and elbow with gradual loading).	Fracture is clinically healed. Physiotherapy to regain full range of motion and strength. Movements should be within the threshold of pain.
**Surgical**		
Phase 1 (0 weeks)	Apply immobilization device. (Wrist and fingers are recommended to be moved within immobilization device for anti-edema).	Immobilization device should not be taken off (dressing, hygiene). Await date of surgery.
Phase 2 (0–2 weeks)	Surgical treatment. Physiotherapy can be introduced. (Unrestricted active range of motion, unloaded).	Patients allowed to lift objects, equivalently to a can of milk (max 1 kg). Caution due to wound healing
Phase 3 (6 weeks)	Continue physiotherapy. (Unrestricted active range of motion, starting gradual loading).	Movements should be within the threshold of pain
Phase 4 (7 weeks)	Continue physiotherapy. (No restrictions, active range of motion with full load).	Physiotherapy to regain full range of motion and strength

### Criterias for early crossover

Patients can be offered to undergo early crossover fixation with a surgical procedure of the surgeon’s choice, if one of these criteria are met:Unacceptable pain experienced by the patientSevere pain with gross instability of the fracture site assessed by:Unable to en bloc elevate the arm due to clear fracture instabilityGentle manipulation of the fracture site. Gentle manipulation should respect the risk of callus breakageSevere problems tolerating the brace, e.g., discomfort, skin irritation, wounds, and hygiene problems.

The patients that undergo early crossover surgery will have the reason for crossover thoroughly noted. We anticipate the surgical procedures will be similar to the ones previously mentioned with the possible addition of bone graft.

### Randomization

A computerized database software, Research Electronic Data Capture (REDCap)© [38] will be used to generate an irreversible random allocation sequence and perform block randomization with selected block sizes of 2 and 4, which will be stratified on site and age (18–64 and +65). Patients will be assigned to the trial with an allocation of 1:1 to either surgical treatment or non-surgical treatment. The trial worker acquires the allocated treatment from the central coordinator with randomization rights to REDCap. The trial worker then initiates the treatment, either by scheduling the surgery date or applying the chosen non-surgical method.

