To our knowledge, four RCTs have been completed and all trials compared plate osteosynthesis to non-surgical treatment by DASH score and without distinction of age [13, 22–24]. Four RCT protocols [25–28] are registered in clinicaltrials.gov, WHO and ISRCTN registry. Two RCT protocols are comparing plate osteosynthesis to non-surgical treatment and the last two RCT protocols are comparing plate and nails to non-surgical treatment. Adults of all ages are included, except in one RCT protocol [27] that has an upper age limit at 65 years. Furthermore, in one already finished trial, the trial design had to be adjusted from an RCT to a prospective non-randomized comparative trial due to treatment allocation problems as there was a strong physician preference towards the surgical treatment option [29]. A Cochrane review could not demonstrate any difference in union rate between different surgical procedures (intramedullary nail and plate osteosynthesis) [30].

This emphasizes the need for a pragmatic approach of interventions by including usual care of surgical treatment, considering the influence of age as well as accepting early secondary surgery as a part of treatment to improve disability and function after 12 months.

The SHAFT protocol conforms with the Standard Protocol Items: Recommendations for Interventional Trials (SPIRIT) [31, 32].

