### Blinding

The trial will consist of several levels of blinding:The primary outcome will be blinded to everyone involved in the trial, apart from the patients and a central trial worker (non-physician), who will only review the questionnaire for completion in REDCapThe statistical analysis will be conducted by a blinded biostatistician

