Recruitment of 287 humeral shaft fractures presents a challenge in a randomized setting as the annual incidence rate is 14.5 per 100.000 [54]. To overcome this, we will be recruiting from multiple sites across 3 Scandinavian countries with comparable healthcare systems and with cultural and demographic similarities. Despite these overall similarities, surgical management can differ from site to site. To prevent against bias in the surgical group, the randomization will be stratified by the study site. One drawback of this type of stratification can be the risk of open blocks in multiple sites, which can give rise to allocation bias. To limit this the randomization will be conducted in small permuted blocks.

One RCT demonstrated a statistically significant difference in a subgroup analysis between the late surgical crossover and primary surgical treatment after 12 months, favoring early surgery, with respect to possible confounding [13]. The research group has furthermore in a recent study showed the same difference between a late surgical crossover and primary successful treatment after 2 years [15]. To avoid prolonged failed treatment courses, and to minimize overall nonunion rates, the trial has implemented an option of early crossover of non-surgical treatment, if certain criteria for delayed union are met. The criteria for early crossover surgery are identical for each age group but differ regarding the time of crossover. The term “early crossover” and “delayed union” were discussed intensively by the study group. “When has the treatment failed?” Crossover to surgical treatment after non-surgical treatment is not uncommonly performed within 12 weeks for the young and is described due to lack of healing and early non-surgical failure [58, 59]. One can argue that a portion of these patients will unite without intervention [60], but multiple studies have currently shown an association between gross mobility from the fracture site to nonunion in a young population after 6 weeks [17, 50, 60]. For the elderly, our clinical experience is that healing first can be anticipated after 12 weeks. We therefore defined delayed union in SHAFT-Y between 6 and 12 weeks and SHAFT-E between 12 and 26 weeks. Furthermore, endpoints were established to create a clear timepoint of when a treatment has failed, which we believe the orthopedic society needs, since there is no consensus in nonunion for humeral shaft fractures [9, 12, 14, 61].

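### Blocks of 2 and 4 within site and age raise correct guessing of the next arm to about 72%, yet the protocol presents small blocks as the limit on allocation bias

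*Protocol article*

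**What the plan says.** Protocol article, Randomization: allocation is 1:1, stratified by site and by age group (18–64 and 65 or over), and the software will "perform block randomization with selected block sizes of 2 and 4". The section does not say whether the order of block sizes is random or whether sites are kept from knowing it. On release it says: "The trial worker acquires the allocated treatment from the central coordinator with randomization rights to REDCap". That worker then starts treatment, "either by scheduling the surgery date or applying the chosen non-surgical method", so the arm is visible locally from then on.

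Protocol article, Blinding: the primary outcome data and the statistician are blinded. Patients know their treatment, and no masking of treating staff is described.

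Protocol article, Recruitment: staff inform eligible patients in the emergency department. Research staff see them at an appointment within 10 days, and randomization follows at once if written consent is given.

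Protocol article, Discussion: stratifying by site is said to risk open blocks at several sites and hence allocation bias. The remedy follows: "To limit this the randomization will be conducted in small permuted blocks".

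Protocol article, Background and rationale: a finished trial of this question had to give up randomization because "there was a strong physician preference towards the surgical treatment option".

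**The concern.** Two properties of a blocked list pull against each other. Short blocks keep the arm totals close at every point, including when a list stops part-way through a block. For the same reason they let anyone who has seen the past allocations infer the next one. Allocation bias in its usual sense, meaning selection of patients in the light of the expected arm, comes through that second route. The Discussion names this bias and then proposes a remedy that increases the opportunity for it.

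A person who expects a particular arm next can bring forward, delay or not book a patient, or can apply the judgement-based exclusion for health conditions preventing either treatment with that arm in mind. The primary analysis is a univariable regression of DASH on treatment, so any resulting difference in case mix would enter the main estimate. The adjusted model in the Secondary analysis section can correct only for the factors it lists.

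**Working it through.** The protocol states no predictability figure, so there is none to reproduce.

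**Inputs.** From Randomization: block sizes 2 and 4, 1:1, within site and age group. Assumptions: the two sizes are equally likely and in random order; the guesser knows which sizes are in use (they are published) and always guesses the arm that is behind, or tosses a coin when the arms are level.

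**List length.** The number of sites is not given. With 5 to 30 equal sites, 163/5 = 32.6 down to 163/30 = 5.4 patients per site in SHAFT-Y, and 124/5 = 24.8 down to 124/30 = 4.1 in SHAFT-E. Ten sites give 16.3 and 12.4. A list of 14 is used as a mid-case.

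**Long-list values, by hand.**
- Block of 2: expected correct guesses 1/2 + 1 = 1.5 of 2 (75%).
- Block of 4: 1/2 + 2/3 + (2/3 × 1/2 + 1/3 × 1) + 1 = 2.833 of 4 (70.8%).
- Equal mix: (1.5 + 2.833)/6 = 72.2% correct overall.
- The list is unbalanced at 1 enrollment per block of 2 and at 1 + 1/3 + 1 = 2.333 per block of 4, so 3.333/6 = 55.6% of the time. Correct guesses at those points are 1 and 2/3 + 1/3 + 1 = 2, so 3/3.333 = 90%.
- Certain allocations, order hidden: only a lead of two proves a block of 4, and the remaining two are then fixed. (1/3 × 2)/6 = 11%.
- Certain allocations, block starts known but sizes not: (1/3 × 2 + 2/3 × 1)/6 = 22%.
- Certain allocations, every block size known: one half in blocks of 2, one third in blocks of 4.

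**Simulated 14-patient list.**

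| Sizes | List unbalanced | Correct when unbalanced | Correct overall | Certain, order hidden | SD of final difference between arms |
|---|---|---|---|---|---|
| 2, 4 | 55% | 89% | 72% | 10% | 0.7 |
| 4, 6 | 60% | 80% | 68% | 6% | 1.0 |
| 4, 6, 8 | 63% | 77% | 67% | 2% | 1.05 |

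The overall rate is the unbalanced share times its hit rate, plus half of the rest. For 2 and 4: 0.55 × 0.89 + 0.45 × 0.5 = 0.71, or 0.72 before rounding. With block starts known, about 20% of allocations are certain for 2 and 4 at this length.

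**Sensitivity.** For lists of 6 to 20 patients, with blocks of 2 making up one third to two thirds of all blocks, overall guessing stays at about 70–73% and certain allocations with order hidden at about 6–13%.

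**Direction.** For fixed, known block sizes, correct guessing is 75% (2), 70.8% (4), 68.3% (6) and 66.6% (8). Smaller blocks are always more predictable.

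**The case against.** The strongest reply is that the Discussion is really about unfinished blocks at many sites. Those cause numerical imbalance, which small blocks do limit, so allocation bias may be loose wording for imbalance. That reading is possible. If it is right, the sentence needs a change of term, and predictability is then not addressed in the article.

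Safeguards also exist and count. A central coordinator releases each allocation, and consent precedes randomization. A tracker would have to follow two age lists per site for an uncommon fracture and act within the 14-day treatment limit. These measures conceal the list itself. They do not stop someone inferring the next arm from past ones before a patient is approached or booked.

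Three stronger readings are tempting but unsupported:
- A reader might take 89% as the guessing rate. It applies only when the list is already unbalanced, and larger blocks are unbalanced more often, so comparing 89% with 80% or 77% overstates the gain.
- A reader might say that each block of 2 makes its second allocation certain. That needs the block's size to be known. With the start known and the sizes equally likely, the other arm follows with probability 1/2 × 1 + 1/2 × 2/3 = 5/6.
- A reader might infer that all site staff see every past allocation, or that selective enrollment will happen. The article says neither, and the physician preference it reports concerns another trial.

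**Conclusion.** The point holds as a correctable design weakness of modest size. Blocks of 2 and 4 raise correct guessing from 50% to about 72%, with about 10% of allocations certain if the order of sizes is hidden and about 20% if block starts are known. On the ordinary meaning of allocation bias, the safeguard named in the Discussion works in the wrong direction.

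The figures rest on an assumed 14-patient list, equally likely sizes in random order, and a person who tracks the list. The documents do not allow the resulting bias in DASH to be quantified, and nothing in them shows that allocation has been or will be subverted. Moving to blocks of 4 and 6 gains about 4 percentage points in overall guessing at 14 patients, and about 3 in a long list: (2.833 + 6 × 0.683)/10 = 69.3% against 72.2%. The share of certain allocations falls from about 10% to 6% with the order hidden.

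**What to change.** 1. For allocation lists not yet used, drop block size 2 and use randomly varying blocks of 4 and 6. Keep the sizes and their order with the list generator, and out of site documents and publications, until recruitment ends.
2. Correct the Discussion to say that small blocks limit numerical imbalance from unfinished blocks and do not limit predictability. Name central release and consent before randomization as the measures that protect concealment.
3. Add site to the adjusted analysis. The primary model is univariable, and the covariates listed under Secondary analysis (age, sex, smoking, alcohol, UCLA activity, ASA grade) leave out site, although it is a stratification factor.

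**Cost.** New allocation tables for unused lists, one wording change and one model term. The price in balance is small: the SD of the final difference between arms in a 14-patient list rises from about 0.7 to about 1.0 patients. Sample size, eligibility and treatment are unaffected. Since the article calls the sequence irreversible, the sponsor should first confirm which lists can still be replaced. Where none can, items 2 and 3 still apply, and the order of block sizes should still be withheld from sites.
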